**Secondary study aims:**

To evaluate the feasibility, potential clinical utility, and cost-effectiveness of a population-based genetic testing strategy for BC precision prevention.

**Secondary outcomes:**

- Clinical utility and effectiveness of the genetics-based personalized precision prevention.
- Cost-effectiveness of the genetics-based personalized precision prevention.
- Feasibility of the genetics-based personalized precision prevention.
- Acceptability, values, preferences, and social norms for personalized precision prevention.
- Equitable accessibility of genetics-based personalized precision prevention.
- Health-care system readiness for the implementation of personalized precision prevention.
- Results of high and moderate risk genetic testing (BRCA1, BRCA2, TP53, STK11, PTEN, CDH1, ATM, PALB2, CHEK2, NBN, NF1).
- Results of SNPs testing and SNP PRS analyses.
- PRS risk versus breast density.
- Individuals' distribution into risk groups.
- Individuals' participation rate from additional counselling; analysis of patients' compliance.
- Exact analysis and description of medical activities after counselling.
- The number of family members invited to additional counselling and their participation rate.
- Costs analysis of all activities.

**Effectiveness and clinical utility of the genetics-based personalized precision prevention.**

Clinical utility refers to the usefulness, benefits, and harms of an intervention. Clinical utility is a multidimensional construct covering effectiveness and cost-effectiveness, as well as the psychosocial, ethical, and legal implications of an intervention. Risk assessment per se does not have inherent clinical utility; the subsequent adoption of a risk-based intervention based on the results of the assessment is what influences the health outcomes. The use of such a strategy depends on whether the risk-based intervention is appropriate, accessible, practicable and acceptable.

**Cost-effectiveness of the genetics-based personalized precision prevention.**

We will use modelling of cost-effectiveness with input data from the clinical pilot project, epidemiological data, relevant healthcare services and their cost data.

**Feasibility of the genetics-based personalized precision prevention**

Feasibility will be investigated by conducting the clinical pilot project describing the process, organization, and results of the applied model of personalized precision prevention.

**Acceptability, values, preferences, and social norms for personalized precision prevention**

Acceptability and preferences will be investigated using relevant questionnaires for:

- Women included in the clinical pilot project.
- Medical personnel involved in processes of personalized prevention.

**Equitable accessibility of the genetics-based personalized precision prevention**

Equitable accessibility will be investigated by conducting the clinical pilot project and describing the process, organization, and results of the applied model of personalized precision prevention.

**Healthcare system readiness for the implementation of personalized precision prevention**

Healthcare system readiness will be investigated by conducting the clinical pilot project and describing the process, organization, and results of the applied model of personalized precision prevention.

## **5. STUDY DESIGN**

General population-based cohort study combined with modelling studies.

The target number of study participants: 80.

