| Study Design                    | A pilot cohort study                                                                                                                                                                                                                                                                                         |                                                                                                                                                                                                                                                                                                                                                                                                                                                                                                                                                                                                                                                                                 |
| Study Participants              | Healthy women at age 40 - 49                                                                                                                                                                                                                                                                                 |                                                                                                                                                                                                                                                                                                                                                                                                                                                                                                                                                                                                                                                                                 |

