#### **4. OBJECTIVES AND OUTCOME MEASURES**

The general aim is to perform a clinical cohort study that would test issues regarding the deployment of PRS test AnteBC and MPV-based risk testing in the Norwegian clinical setting. This clinical pilot would simultaneously evaluate logistical and ethical considerations (patient risks, feedback, operational procedures), test the flow of information, and would also create prospective performance data for PRS testing. In addition, the project will explore the relationship between PRS and mammographic density (MD).

The target group is healthy women at age 40-49, which is the age group before the current official screening. For genetic risk prediction, the project uses PRS and, if indicated, MPV tests as healthcare services with the following diagnostic screening and prevention activities.

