### **5.1. Study Participants**

#### **Inclusion Criteria:**

- A study group of women at age 40-49 (women currently not invited into regular BC screening), who are referred to clinical mammography and no sign of malignancy after mammographic assessment.

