### **5.2. STUDY PROCEDURES AND RECRUITMENT**

Women referred to clinical mammography and no sign of malignancy after assessment, will be asked to participate in the study. These women are referred to mammography due to clinical symptoms, like breast lumps, pain, and nipple discharge. Women referred due to symptoms may have an increased risk for BC, compared to women without symptoms. Further, women with dense breast tissue have a higher risk of BC than women with less dense breasts.

Participation in the study is not solely limited to women referred to clinical mammography in Vestre Viken. However, we will not actively recruit women outside the Vestre Viken hospital area, but may include these women after a personal request from the women.

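### The design is labelled general population-based, but entry is by referral for breast symptoms (plus an unclear personal-request route), so the primary proportion and the acceptability result describe a narrower group than the label says

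*Protocol*

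**What the plan says.** Protocol section 5 gives the design as a "General population-based cohort study combined with modelling studies" with a target of 80 participants. The synopsis names the participants as "Healthy women at age 40 - 49", and section 4 states: "The target group is healthy women at age 40-49, which is the age group before the current official screening".

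The inclusion criterion in section 5.1 is narrower. It takes women of that age "who are referred to clinical mammography and no sign of malignancy after mammographic assessment". Section 5.2 explains why they were referred: "These women are referred to mammography due to clinical symptoms, like breast lumps, pain, and nipple discharge". It adds: "Women referred due to symptoms may have an increased risk for BC, compared to women without symptoms". For women outside the hospital area, who are not actively recruited, the same section says the team "may include these women after a personal request from the women".

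The primary outcome in section 4 is the proportion of women with elevated risk, broken down by PRS, monogenic result and high breast density. Acceptability is to be asked of "Women included in the clinical pilot project" and of the medical staff involved.

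**The concern.** A prevalence means something only for a defined population. The label in section 5 points to women aged 40-49 at large, while the entry rule points to women with a breast complaint whose work-up was negative. The protocol itself grants that the two groups may differ in risk, but it neither narrows the claim nor plans a comparison with the wider population.

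The information that would let a reader judge the selection is also mostly not planned. Neither reason for referral nor route of entry is in the assessment and variable lists of section 5.4, and no count of women approached or declining is foreseen. If these are not captured at recruitment, they are largely lost.

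At stake are the reading of the primary result, the reading of acceptability, and the use of pilot data in the cost-effectiveness model (section 4).

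**Working it through.** The protocol gives no expected prevalence, consent rate or precision target, so it has no figure of its own to reproduce. The check is a comparison of passages, followed by an illustration on stated assumptions.

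**Passages side by side**

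| Item | Where | What it fixes |
|---|---|---|
| Design label | 5 | general population |
| Entry rule | 5.1 | referred to clinical mammography, no sign of malignancy |
| Why referred | 5.2 | symptoms; possibly raised risk |
| Second route | 5.2 | personal request from outside the area; link to 5.1 not stated |
| Primary outcome | 4 | proportion at elevated risk (PRS, monogenic, density) |
| Women asked about acceptability | 4 | those enrolled, hence consenting |
| Referral reason, entry route | 5.4 | not listed |
| Women approached or declining | 4, 5.4, 6.2 | not counted; the participation rates listed concern additional counselling and family members |

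The components of the primary outcome are not equally exposed. PRS is measured in every participant, and nothing in the protocol shows that it differs in symptomatic women. Monogenic testing is done only in women who meet national criteria (5.2, Step 2), which rest largely on family history, so its yield depends on who enters. Density is read in women examined for symptoms.

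**Illustration 1: shift in a proportion.** Assume a population proportion p and an odds ratio OR for elevated risk in entrants against the population. The expected proportion among entrants is OR·p / (1 − p + OR·p). With p = 0.20 (assumed):

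- OR 0.5: 0.10 / 0.90 = 11.1%
- OR 0.8: 0.16 / 0.96 = 16.7%
- OR 1.25: 0.25 / 1.05 = 23.8%
- OR 1.5: 0.30 / 1.10 = 27.3%
- OR 2.0: 0.40 / 1.20 = 33.3%

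Odds ratios on both sides of 1 are shown because the protocol does not settle the direction. For comparison, an observed 16/80 (20%) has an exact 95% interval of 11.9% to 30.4%. That interval covers sampling error only and would not reveal a shift of this kind.

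**Illustration 2: acceptability.** Assume a share c of eligible women approached consents and 90% of those consenting approve. With nothing known about decliners, approval among all women approached lies between 0.9c and 0.9c + (1 − c):

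- c = 0.8: 72% to 92%
- c = 0.6: 54% to 94%
- c = 0.4: 36% to 96%

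Without a count of decliners, c itself is unknown.

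**The case against.** The strongest reply is that this is a pilot and mostly says so. The title, the synopsis and the research methodology paragraph all use pilot wording, the analysis is mainly descriptive, and section 5.2 openly says referred women may be at higher risk. In the primary aim, population-based describes the testing strategy under study and not the sample, and a pilot may examine such a strategy in a convenience sample. Healthy can fairly mean free of cancer, which agrees with the entry and exclusion criteria. All of this stands. It reduces the outright error to the label in section 5, but it does not make that label right or say to whom the primary proportion applies.

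Several stronger readings are tempting and not supported:

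- **That the bias favours the programme.** The exclusion of known hereditary syndromes and of women already tested could lower the monogenic yield, and the referral reasons named are symptoms, not family history.
- **That self-requesting women bypass the referral rule, or come because of family history.** Section 5.2 can be read as admitting women referred elsewhere who still meet 5.1, and it gives no motive. It is unclear, and no more can be said.
- **That the selection cannot be described at all afterwards.** Postal address would identify out-of-area women, and family and personal medical history are collected. A partial description is possible; referral reason and decliners are what is missing.
- **That the PRS distribution of these 80 women drives the economic model.** Section 4 says only that pilot data are among the inputs, together with epidemiological, service and cost data.
- **That acceptability is misdescribed.** The protocol says plainly that enrolled women are asked, and staff are surveyed as well. Staff answers do not, however, supply the views of women who declined.

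**Conclusion.** The point holds in a limited form. The section 5 label conflicts with the entry rule in 5.1 and the account in 5.2, and the personal-request route is not tied to the entry rule. The primary proportion, above all its monogenic and density parts, cannot be taken as a general-population prevalence, and acceptability among women is conditional on consent.

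The direction and size of any bias are unknown. The figures above rest on assumed prevalence, odds ratios, consent and approval. They show only that moderate selection could move a 20% proportion by several points either way, and that approval among all women approached is weakly bounded when consent is incomplete. The conflict between passages needs no assumption. The matter should be corrected, but it does not undermine the study as a pilot.

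**What to change.** 1. In section 5, replace the label with wording such as: cohort of women aged 40-49 referred to clinical mammography, without sign of malignancy, recruited mainly in the Vestre Viken area. State the primary proportion for that population. Mainly is needed because 5.2 allows women from elsewhere.
2. Reconcile 5.2 with 5.1: say whether women who join on personal request must meet the referral criterion.
3. Add reason for referral and route of entry to the variables in 5.4, and report the primary outcome with and without self-requesting women.
4. Keep an anonymous count of eligible women approached and declining, and report uptake next to acceptability.
5. Where pilot proportions enter the cost-effectiveness model, say that they come from a referred, consenting sample, and vary them in the sensitivity analysis already planned in 6.2.

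The cost is two variables, a tally at the breast centre, some rewording and a narrower claim. No extra participants or tests are needed.

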### **5.1. Study Participants**

#### **Inclusion Criteria:**

- A study group of women at age 40-49 (women currently not invited into regular BC screening), who are referred to clinical mammography and no sign of malignancy after mammographic assessment.

#### **Exclusion Criteria:**

- Women with already diagnosed malignancies or hereditary cancer syndromes.
- Signs of malignancy after mammographic assessment.
- Women already tested for MPVs and PRSs.
- Ashkenazy Jewish ethnicity.

#### **Research methodology**

We will use a pilot feasibility cohort study approach, collecting data from the study and adding modelling clinical efficacy and cost-effectiveness analyses.

The pilot feasibility study implements the program of the genetics-based personalized BC prevention and screening for healthy women.

### **5.2. STUDY PROCEDURES AND RECRUITMENT**

Women referred to clinical mammography and no sign of malignancy after assessment, will be asked to participate in the study. These women are referred to mammography due to clinical symptoms, like breast lumps, pain, and nipple discharge. Women referred due to symptoms may have an increased risk for BC, compared to women without symptoms. Further, women with dense breast tissue have a higher risk of BC than women with less dense breasts.

Participation in the study is not solely limited to women referred to clinical mammography in Vestre Viken. However, we will not actively recruit women outside the Vestre Viken hospital area, but may include these women after a personal request from the women.

#### **STEP 1. Information**

Information about the genetic-based BC precision prevention possibilities is provided to the women at the breast centre.

The women will be asked for study participation and asked for informed consent for personalized screening and prevention.

## **STEP 2. Genetic testing / Risk evaluation**

A recommendation on the level of the genetic test is given, variants:

- All women: PRS testing. Genotyping is performed using the AnteBC test with a non-invasive saliva-based method to collect and isolate a patient's DNA. Antegenes performs the risk assessment based on imputed genotype data.
- In addition: questionnaire about genetic and cancer family history.
- Women that fulfill standard criteria according to national guidelines will be submitted to genetic counselling and testing of monogenic germline pathogenic variants (MPV), see chapter 3.2 for criteria.

After the patient's **informed consent**, an AnteBC test is performed and, if indicated, a patient is directed also for **MPV testing**.

## **STEP 3. Recommendations based on results of genetic testing/risk evaluation**

### **Recommendations based on PRS test:**

Based on the PRS, it is possible to divide the patient's relative risk of developing BC into different levels compared to the average in the given age, while accurately assessing the risk of a particular percentile.

Different Levels of Disease Risk:

- Lower or at the same level.
- Slightly elevated (up to two times).
- Moderately elevated (two to three times).
- Elevated more than three times.

### **Applying the logic of the model:**

In Norway, mammography screening in the age group 50-69 years at two-year intervals is currently a recognized standard practice. Consequently, the "zero point" of the risk level at the beginning of the screening is the average risk level of 50-year-old women. We can conclude that currently in Norway BC screening mammography is an accepted and publicly funded early BC detection measure for women in the age group 50-69, where the average BC 10-year risk at age 50 is 2.1% using NORDCAN data (<https://www-dep.iarc.fr/NORDCAN/english/frame.asp>) and iCARE absolute risk calculation (7).

Patient's individual and patient's population average 10-year BC risks are reported in the AnteBC test report.

When assessing individual risk levels, the above risk groups can be advised based on current scientific knowledge:

### **Variant 1. If the risk is below average or at a medium level:**

- Participate in a standard mammography screening from the age of 50.

### **Variant 2. If the risk is slightly increased - up to two times (moderate increase in risk depending on age):**

- Implement mammography screening at **two-year intervals** from the age at which the risk of the average 50-year-old woman is reached (depending on the age at which the 10-year risk reaches 2.1 %), i.e. screening is recommended for those under 50 years of age due to an increased risk.

**Variant 3. If the risk is increased two to three times (moderate increase in risk compared to the same age average):**

- Implement mammography screening at **two-year intervals** from the age at which the risk of the average 50-year-old woman is reached (depending on the age at which the 10-year risk reaches 2.1 %).

and/or

- Implement mammography screening at one-year intervals from the age at which the average 50-year-old woman reaches twice the risk level (depending on the age at which the 10-year risk exceeds twice the corresponding age level or for women under 50 from the risk level of  $2 \times 2.1$  %, which is twice the risk level for women aged 50);

**Variant 4. If the risk has increased more than three times the average (high-risk increase):**

- Implement mammography screening at **two-year intervals** from the age at which the risk of the average 50-year-old woman is reached (depending on the age at which the 10-year risk reaches 2.1 %)

and/or

- Implement mammography screening at one-year intervals from the age at which the average 50-year-old woman reaches twice the risk level (depending on the age at which the 10-year risk exceeds twice the corresponding age level or for women under 50 from the risk level of  $2 \times 2.1$  %, which is twice the risk level for women aged 50);

**Recommendations based on MPV test:**

No MPVs detected: approach according to **the PRS test recommendations**.

MPV detected: additional genetic counselling and approach according to **the national guidelines for MPV management (see Chapter 3.2.)**:

- Patient counselling by a medical geneticist, family mapping, and cascade testing.
- The patient is referred to a gynecologist/breast cancer specialist according to national guidelines.
- Treatment of increased risk at the health care provider level according to national guidelines: personalized prevention is implemented.

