### ***Current practices of BC MPV testing in Norway***

Current criteria for MPV testing are characterized here:

<https://www.helsebiblioteket.no/retningslinjer/brystkreft/forord>

Criteria for genetic testing of BC patients:

- Women diagnosed with BC 60 years or younger.
- Male BC any age.
- Women diagnosed with ovarian cancer at any age.
- Women diagnosed with BC older than 60 years with a family history of cancer as follows:

1) One first-degree relative (or second-degree through a man) with BC, and the mean age of onset is 55 years or younger.

2) Two first-degree relatives (or second-degree through a man) with BC at any age.

3) One first-degree relative (or second-degree through a man) with ovarian cancer.

4) One first-degree relative with prostate cancer 55 years or younger.

A healthy woman can be offered genetic testing if she has a first-degree relative who fulfills any of the criteria above.

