### Follow up of women with an increased familial risk for BC:

Women with a mutation in the high-penetrance genes are offered risk-reducing surgery with prophylactic mastectomy. High-risk women who have not removed their breasts are offered annual screening with mammography and breast MRI from the age of 25 until the age of 70 for women with BI-RADS density category c or d, and 60 for women with a density a or b. Above this age (60/70), the women are offered annual mammography as long as considered appropriate according to general health status.

Women considered to have an increased familial risk for BC without mutations in the high-penetrance genes are recommended annual mammography from 40-60 years. From the age of 50, they are screened every second year in the ordinary screening program and referred for clinical mammography the years

in-between. From the age of 60, they are recommended to participate in the ordinary biennial screening program. No special follow-up is recommended after the age of 70.

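### A negative MPV test leads to PRS advice with no familial-risk floor, so a woman at increased familial risk can be advised less mammography than the national follow-up the protocol describes

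*Protocol*

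**What the plan says.** **Who is tested.** Step 2 of Section 5.2 gives every woman the PRS test and a family-history questionnaire. Women who meet the national criteria also have genetic counselling and MPV testing. For a healthy woman, Section 3.4 gives the criterion: "A healthy woman can be offered genetic testing if she has a first-degree relative who fulfills any of the criteria above".

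**What follows a negative test.** Step 3, under the MPV recommendations, reads "No MPVs detected: approach according to" the PRS test recommendations. National guidelines apply only when an MPV is found. The paragraph on breast density repeats this, with MPV detection as the only exception. Step 4 puts Variants 1 to 4 into practice and names no other route.

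**What the PRS advice is.** Variant 1: "Participate in a standard mammography screening from the age of 50". Variant 2: two-year intervals from the age at which the 10-year risk reaches 2.1%. Annual mammography appears only in Variants 3 and 4.

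**What national follow-up is said to be.** Section 3.4: "Women considered to have an increased familial risk for BC without mutations in the high-penetrance genes are recommended annual mammography from 40-60 years". It continues: "From the age of 50, they are screened every second year in the ordinary screening program and referred for clinical mammography" in the intervening years.

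**The concern.** A woman can be tested because of her family history, carry no detectable variant, and still be at increased familial risk. The protocol accepts this. Section 3.4 puts 15 to 20 percent of breast cancer as familial without an identified mutation and says family history may inform management. Section 3.5 lists family history among the major factors for risk category. The AnteBC assessment, however, is described as resting on imputed genotype data, and no recommendation in Step 3 or Step 4 uses family history.

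Read as written, the rule can move a participant aged 40 to 49 from annual mammography to two-yearly mammography, or to none before 50. That is a participant-safety matter. The information needed to avoid it, her family history, has already been collected when the advice is given.

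**Working it through.** There is no planned figure to reproduce. The check traces the decision path and then counts examinations.

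**1. Is the affected group eligible?** Yes. Inclusion takes women aged 40-49 "who are referred to clinical mammography and no sign of malignancy after mammographic assessment", and that age range lies inside the 40-60 window of the familial follow-up. The exclusions remove "Women with already diagnosed malignancies or hereditary cancer syndromes" and women already tested. An untested woman with a family history remains eligible.

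**2. Does any later step restore the familial follow-up?** No. Step 3 invokes national guidelines only for a detected MPV, and Step 4 refers back to the Variants. Counselling in Step 2 is not linked to the recommendation, and the additional counselling in Step 3 is reserved for carriers.

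**3. How many examinations are at stake?** Conventions: exact one- or two-year spacing from the baseline mammogram, with baseline not counted. Variant 2 is taken at its maximum, with the 2.1% threshold already reached at enrolment. Variant 1 is two-yearly from 50.

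Before age 50:

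| Enrolled at | Annual familial follow-up | Variant 1 | Variant 2, at most |
|---|---|---|---|
| 40 | ages 41-49: 9 | 0 | 42, 44, 46, 48: 4 |
| 45 | ages 46-49: 4 | 0 | 47, 49: 2 |

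Over the 10-year follow-up stated in Step 4:

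| Enrolled at | Annual familial follow-up | Variant 1 | Variant 2, at most |
|---|---|---|---|
| 40 | ages 41-50: 10 | 50: 1 | 5 |
| 45 | ages 46-55: 10 | 50, 52, 54: 3 | 5 |
| 49 | ages 50-59: 10 | 50, 52, 54, 56, 58: 5 | 5 |

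If an examination in the year of entry is counted instead, the figures before 50 become 10, 0 and at most 5 (entry at 40) and 5, 0 and at most 3 (entry at 45). The direction is unchanged.

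**4. How high must the PRS be to match annual follow-up?** For women under 50, one trigger stated in Variants 3 and 4 is 2 × 2.1% = 4.2%. The protocol does not give the average 10-year risk below 50. Assuming 1.2% to 2.0%:

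- Annual advice by that trigger needs a relative risk of 4.2/1.2 = 3.5 down to 4.2/2.0 = 2.1.
- Two-yearly advice needs 2.1/1.2 = 1.75 down to 2.1/2.0 = 1.05.

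On this reading, a woman below the first figure is advised less than annual mammography, and a woman below the second has no screening advised yet at her current age.

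**The case against.** **The group is undefined and may be small.** Section 3.4 gives criteria for MPV testing, not for annual familial follow-up, so a woman can qualify for the test and not for the follow-up. Most participants are referred for symptoms, and women already tested are excluded. This stands as a limit on frequency. It narrows the group without emptying it: a symptomatic, untested woman with a family history can enter, and Section 5.2 also admits women on personal request.

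**Usual care and counselling would catch it.** No text withdraws usual care, and a geneticist could well keep a woman on annual mammography. But nothing says PRS advice is only additional, and nothing carries a familial-risk judgement from counselling into Step 3. The exception for detected MPVs is repeated under the density heading, which is not where a general rule would be expected, yet Steps 3 and 4 state the PRS route without any familial condition. The examinations Step 4 calls extra are extra to the screening programme, not to familial follow-up.

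**Variants 3 and 4 may already give annual mammography.** This is largely fair. They also offer a trigger of twice the risk for the woman's own age, which a woman at two to three times the average would meet. Whether 4.2% replaces that trigger under 50 is unclear, and the annual option is joined to the two-yearly one by an and/or. The finding therefore rests on Variants 1 and 2.

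Carriers of moderate-risk variants are not affected, because any detected MPV leads to national guidelines.

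**Conclusion.** The concern holds. For an MPV-negative woman considered at increased familial risk, the Step 3 rule as written gives less mammography in Variant 1 or 2 than the national follow-up in Section 3.4. For entry at 40, the shortfall before 50 is about 9 examinations in Variant 1 and at least 5 in Variant 2 (9 − 4). Over ten years it is 9 (10 − 1) and at least 5 (10 − 5). These counts describe one woman under exact spacing; how many women are affected cannot be worked out from the protocol. The primary outcome, the proportion at elevated risk, is not affected. The change should be made because it protects participants and costs little.

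**What to change.** 1. Replace the negative-test rule in Step 3 with: *No MPV detected: follow the more intensive of the PRS recommendation and the national follow-up for increased familial risk (annual mammography from 40, Section 3.4), as judged at genetic counselling.*
2. Add to the paragraph that applies PRS advice to all density categories: *PRS-based advice adds to, and never reduces, follow-up indicated by national guidelines or by the radiologist.* This also covers women who were not MPV-tested. The mention of the radiologist is a precaution; the finding does not depend on it.
3. In the same edit, correct the two pointers to Chapter 3.2 in Steps 2 and 3. The testing criteria and follow-up rules are in Section 3.4; Section 3.2 describes the screening programme. This is clerical.

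The cost is two sentences and two cross-references. Family history is already collected and counselling is already planned, so no new procedure is needed. Some women may be offered more clinical mammograms than under the current rule, but no more than the national follow-up already described for them.
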